#### 2.4.3. Effectiveness Outcomes

Effectiveness outcomes include women’s depression symptoms (primary), coping behaviours, self-efficacy, perceived support levels, intimate relationship satisfaction, post-abortion personal growth, and abortion-relevant outcomes. Specific measures include:

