##### Depression

Changes in women’s depression symptoms will be measured by the Patient Health Questionnaire (PHQ-9) [25]. The nine-item scale will be administered at the initial patient interview and monitor progress. Participants will be asked to rate the severity of their depressive symptoms on a four-point scale (0 = not at all; 1 = several days; 2 = more than half the days; and 3 = nearly every day). The nine items cover symptoms associated with experiencing pleasure, feeling down, and self-esteem. The total score can range from 0 to 27, with higher scores indicating greater severity of depression. The tool has been translated and validated with the Chinese population, showing strong psychometric properties (α = 0.86) [26].

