### 2.8. Data Collection

Data collection will occur at five timeframes: T-0, during recruitment before randomization; T-1, on abortion day before discharge (normally 2 h post-abortion procedure); T-2, during women’s post-abortion exam visit, normally 2 weeks post-abortion; T-3, 6 weeks post-abortion; and T-4, post completion of all follow-ups of all participants. See Table 3 for detailed information on data collection, including What, Who, When, Where, How, and by What data.

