### 2.9. Data Analysis

Participant characteristics, feasibility outcomes, and quantitative acceptability outcome data will be summarized with descriptive statistics, including frequency counts and percentages (categorical variables) and mean with 95% confidence intervals (CIs) or standard deviation (continuous variables). Intervention feasibility and acceptability will be assessed against the following criteria: eligibility: ≥60% of patients screened will be eligible; recruitment: ≥80% of eligible participants will agree to participate; protocol fidelity: ≥90% of patients randomized to each group will receive the allocated intervention; retention: <20% of patients will be lost at 6 weeks after abortion; and missing data: <20% of data will be missing. Between-group differences of participant characteristics, baseline data, and effectiveness outcomes will be detected using Statistical Package for the Social Sciences (SPSS)^®^ version 23 [41]. Specifically, Chi square tests will be used for categorical/dichotomous variables, and *t*-tests or Mann–Whitney U tests for continuous variables (depending on normality). To capture changes in the effect outcomes over time, a general linear regression analysis will be performed. See Table 3 for the specific analysis approaches.

For qualitative data, audiotapes of telephone interviews will be transcribed and de-identified by the primary researcher. Transcripts and notes will be analyzed using the deductive approach of content analysis [42]. First, a structured analysis matrix will be developed based on the aims of the study and the TFA of Health Care Intervention. Then the primary researcher and nurse coordinator will independently review all de-identified data, and content fit the matrix. They will work together to group similar content within the matrix boundaries as categories, and then main categories. After abstraction of each category, the primary researcher and nurse coordinator will make a joint decision on how to model and report the results. Any discrepancies along the process will be discussed with a third reviewer until an agreement is reached. To preserve the original meaning of women’s statements, the data analysis process will be conducted using Chinese. Development of the analysis matrix and reporting process will use Chinese and English to reduce potential bias and build a shared vision among the research team.

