## 3. Discussion

We propose a two-armed randomized trial among Chinese women undergoing abortion, to assess the feasibility, acceptability, and potential effects of the START intervention. To our knowledge, this study will be the first trial to address Chinese abortion patients’ psychological wellbeing by providing a comprehensive supportive intervention based on the Transactional Model of Stress and Coping [19]. This innovative intervention contains different active components that will be delivered using different methods. Findings from this trial will allow us to evaluate the feasibility and acceptability of the intervention, which will inform intervention refinement [17]. The findings will also help to identify potential barriers and facilitators for implementing the intervention in the Chinese context [43]. As the preliminary effectiveness and effect of the intervention will also be described, the study could have important implications for relevant policymakers, practitioners, researchers, or other stakeholders [44].

We are employing a rigorous study design to ensure the internal and external validity of findings. This trial responds to the call for well-designed, rigorously conducted scientific research in abortion care in developing countries [1]. Randomization and statistical analysis adjusted for any difference in baseline characteristics between groups will protect against selection bias, and ultimately warrant internal validity [45]. The study will be performed under real-world clinical practice conditions, which will enhance the external validity and generalizability of results. All instruments used in this study have been validated in the Chinese population, which will also enhance the reliability of findings.

A further strength is that we have adopted a series of appropriate guidelines to ensure the normalization, transparency, and replication of the study. The TIDieR checklist has been used to describe the intervention [23]. Application of the CONSORT statements [20,21] and the SPIRIT 2013 Checklist [22] have been followed.

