**Effectiveness outcomes**				
Depression	T-0, -1, -2, -3	Primary researcher (T0, 3) and nurse coordinator (T-1, -2); at clinic facilities; face to face (T-0, -1, -2) and by telephone (T-3)	SMD-A	Descriptive statistics *t*-test/Mann–Whitney U test comparing baseline to T-3 *t*-test/Mann–Whitney U test comparing differences between groups at T-3 Linear regression measuring change over time
Perceived support	T-0, -1, -2, -3	As above	MOS-SSS	As above
Intimate relationship	T-0, -1, -2, -3	As above	CSI-4	As above
Coping behaviours	T-0, -2, -3	As above	CBCI	Descriptive statistics *t*-test/Mann–Whitney U test comparing baseline to T-3 of each coping style *t*-test/Mann–Whitney U test comparing differences between groups of each coping style at T-2 and T-3
Self-efficacy	T-0, -2, -3	As above	GSE-10	Descriptive statistics *t*-test/Mann–Whitney U test comparing baseline to T-3 *t*-test/Mann–Whitney U test comparing differences between groups at T-2 and T-3
Post-abortion growth	T-2, -3	As above	PTGI-SF	Descriptive statistics *t*-test/Mann–Whitney U test comparing T-2 to T-3 *t*-test/Mann–Whitney U test comparing differences between groups at T-2 and T-3
Abortion outcomes	T-3	As above	Self-design questions	Descriptive statistics Chi Square test comparing differences between groups at T-3

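### The stated between-group tests of the scales ignore the pre-randomization score, and the adjusted analysis cited in the Discussion is tied to no model; naming the T-0 score as covariate would gain precision at almost no cost

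*Protocol article*

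**What the plan says.** Section 2.4.3 makes depression the primary effectiveness outcome: "Effectiveness outcomes include women’s depression symptoms (primary"). Section 2.8 places the first measurement at "T-0, during recruitment before randomization". Table 3 schedules depression, perceived support and intimate relationship at T-0, T-1, T-2 and T-3, and coping and self-efficacy at T-0, T-2 and T-3. Post-abortion growth is measured only at T-2 and T-3.

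For group differences on continuous variables, Section 2.9 gives t-tests or Mann–Whitney "U tests for continuous variables (depending on normality") and refers to Table 3 for detail. The depression row of Table 3 lists a baseline-to-T-3 comparison, then a t-test or Mann–Whitney "U test comparing differences between groups at T-3 Linear regression measuring change over time". Support and relationship follow the same row. Coping and self-efficacy have between-group tests at T-2 and T-3 and no regression entry.

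On the regression, Section 2.9 says only: "To capture changes in the effect outcomes over time, a general linear regression analysis will be performed". Neither place states a group, baseline or covariate term.

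The Discussion (Section 3), in support of internal validity, says that randomization and "statistical analysis adjusted for any difference in baseline characteristics between groups will protect against selection bias".

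**The concern.** Two things do not fit together. First, the only explicit between-group tests of the scales leave out the covariate most likely to predict the outcome: the same scale's score before randomization. Second, the Discussion counts on an adjusted analysis, but nothing in Section 2.9 or Table 3 is described as adjusted. Its wording suggests adjustment triggered by whatever imbalance is seen, not by a covariate named in advance.

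At stake is mainly precision. With about 36 evaluable women per arm, outcome variance that the baseline score explains stays in the error term, and part of any chance baseline imbalance enters the estimated effect. Allocation in blocks of four (Section 2.7) balances numbers, not baseline depression. Section 4 says the results will direct a later fully powered trial, so the effect estimate and its interval matter more here than a p-value. Letting observed normality choose between a t-test and a rank test also lets the data decide whether a mean difference or a rank comparison is reported.

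**Working it through.** **Inputs.** From Section 2.5: standardized effect d = 0.39, two-sided alpha 0.05, power 90%, 72 evaluable women and 90 recruited at 20% attrition. With 1:1 allocation (Section 2), 72 gives n = 36 per arm. The correlation r between the T-0 and T-3 scores is not in the article. I assume 0.3, 0.5 and 0.7.

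**The plan's own figure.** The attrition step reproduces: 72 / (1 − 0.20) = 90. The 72 does not. A two-sample t-test with d = 0.39, two-sided 0.05 and 90% power needs 140 per arm, 280 in total. A total of 72 does arise from a paired test with a standardized difference of 0.39, or a two-group ANOVA with f = 0.39 (equivalent to d = 0.78). That is a separate matter, but it explains the low starting power below.

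**Unadjusted test at T-3.** Noncentrality = d × √(n/2) = 0.39 × √18 = 1.655, with 2n − 2 = 70 degrees of freedom. Power = 37.2%.

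**ANCOVA on the T-0 score.** Residual variance is multiplied by 1 − r². Noncentrality = 1.655 / √(1 − r²), with 2n − 3 = 69 degrees of freedom. In SD units the standard error of the arm difference is √(2/36) × √(1 − r²) = 0.236 × √(1 − r²).

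| Assumed r | Residual variance | Equivalent gain in n, 1/(1 − r²) | Standard error (SD) | Noncentrality | Power at d = 0.39 | d detectable with 90% power |
|---|---|---|---|---|---|---|
| 0 | 1.00 | 1.00 | 0.236 | 1.655 | 37.1% | 0.775 |
| 0.3 | 0.91 | 1.10 | 0.225 | 1.735 | 40.2% | 0.740 |
| 0.5 | 0.75 | 1.33 | 0.204 | 1.911 | 47.0% | 0.672 |
| 0.7 | 0.51 | 1.96 | 0.168 | 2.317 | 62.7% | 0.554 |

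The r = 0 row shows the cost if the baseline score predicts nothing: 37.2% becomes 37.1%. These figures count only the lost degree of freedom. Allowing also for random baseline imbalance, which inflates the variance by about 1 + 1/(2n − 4) = 1 + 1/68 = 1.015, lowers each ANCOVA power by a further 0.4 to 0.6 points and does not change the picture.

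**Chance imbalance.** The standard error of a baseline difference is √(2/36) = 0.236 SD. With similar SDs at both visits, an imbalance carries into the unadjusted T-3 difference by a factor of about r. A one-standard-error imbalance therefore shifts the estimate by:
- r = 0.3: 0.3 × 0.236 = 0.07 SD, or 0.07/0.39 = 18% of the target effect
- r = 0.5: 0.5 × 0.236 = 0.12 SD, or about 30%
- r = 0.7: 0.7 × 0.236 = 0.165 SD, or about 42%

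**Limit of the gain.** At d = 0.39, 90% power by ANCOVA needs 254, 210 or 144 evaluable women in total at r = 0.3, 0.5 or 0.7. With 72 it would need r of about 0.865.

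**The case against.** The strongest defence is that a regression is planned for depression, support and relationship on data that include T-0, and that a condensed article may leave its terms to the analysis plan. That stands in part: the regression could contain group and baseline. It does not cover coping and self-efficacy, which have T-0 scores but no regression in Table 3. Nor does it change the explicit between-group tests, which are unadjusted.

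A reader might infer several stronger points that the article does not support:
- That no adjusted analysis is planned. The Discussion announces one; the gap is that no model or covariate is tied to it.
- That covariates will be picked by baseline p-values. Section 2.9 does test baseline differences, and the Discussion wording makes this plausible, but no text links the two.
- That the T-3 test is the designated primary analysis. Depression is the primary effectiveness outcome and T-3 is its only stated between-group time point, but no analysis carries that label.
- That the unadjusted comparison is biased, or that imbalance enters the estimate in full. Randomization keeps it unbiased in expectation, and imbalance carries over only by about r.

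It is also fair that the gain is modest at the low end (37% to 40% at r = 0.3) and that the trial seeks preliminary efficacy only. That limits the consequence, but a nearly free gain in precision is still worth having. Whether to retain a Mann–Whitney test is a matter of method, not an error, so it can stay in a supporting role.

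**Conclusion.** The point holds as a low-cost improvement and a mismatch to repair, not as a flaw that invalidates the comparison. The explicit between-group tests leave unused a pre-randomization score collected for five of the six scale outcomes, and the adjustment invoked in the Discussion is not specified in the methods. For depression at 36 evaluable per arm and d = 0.39, prespecified adjustment raises power from about 37% to about 40%, 47% or 63%, and cuts residual variance by 9%, 25% or 49%, at r = 0.3, 0.5 or 0.7.

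These figures rest on the assumed r, equal variances, a linear relation between the T-0 and T-3 scores and exactly 72 evaluable women. It would be wrong to conclude that adjustment rescues the sample size: power stays well below the stated 90% throughout this range.

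**What to change.** 1. Settle the depression instrument first: Section 2.4.3 describes the PHQ-9, while Table 3 lists the SMD-A. The covariate cannot be named until these agree.
2. For each scale measured at T-0, make the between-group analysis an ANCOVA with that scale's T-0 score as the prespecified covariate, or a mixed model with arm, visit, arm-by-visit and the T-0 score. Report the adjusted mean difference with its 95% CI. If the listed regression is meant to do this, state its terms and extend it to coping and self-efficacy.
3. Keep any Mann–Whitney test as a sensitivity analysis, so that the normality check no longer decides which quantity is reported.
4. Do not use baseline significance tests to choose covariates.
5. Reword the Discussion to say that the analysis is adjusted for the prespecified baseline score.

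Post-abortion growth has no T-0 score and is not covered by this change. The cost is wording and one residual degree of freedom per model; no new data are needed.

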### 2.5. Sample Size

A formal sample-size calculation is not necessary for research objectives 1 and 2 [20]. For objective 3, G*Power software was used to determine reasonable sample size for the estimation of differences between intervention and control groups. The effect size on depression reported by similar interventions ranged from 0.39 to 1.06 [37,38,39]. G*power indicated a total of 72 participants will be required to detect a 0.39 effect size for depression, two tailed, with alpha at 0.05 and power at 90%. Anticipating a 20% attrition rate, recruitment was set at 90 (45 women per group).

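### Table 3 names an independent-samples test for scores from the same women, and the stated regression for change over time makes no allowance for within-woman correlation

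*Protocol article*

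**What the plan says.** Section 2.9 (Data Analysis) of the protocol article gives two methods for the scale outcomes. The first is t-tests or "Mann–Whitney U tests for continuous variables (depending on normality"). The second, for the time course, reads "To capture changes in the effect outcomes over time, a general linear regression analysis will be performed". The reader is sent to Table 3 for specifics.

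Table 3 (Effectiveness outcomes) has three kinds of entry:

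- **Two time points.** "Mann–Whitney U test comparing baseline to T-3", with a t-test as the alternative, for depression, support, relationship satisfaction, coping and self-efficacy. For post-abortion growth, which has no baseline score, it is "Mann–Whitney U test comparing T-2 to T-3".
- **Two groups.** A separate line, for depression "Mann–Whitney U test comparing differences between groups at T-3". Support and relationship satisfaction follow depression. Coping, self-efficacy and growth are compared at T-2 and T-3.
- **Time course.** "Linear regression measuring change over time", for depression, support and relationship satisfaction only, each collected at T-0, T-1, T-2 and T-3.

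The article names no paired t-test, signed-rank test, mixed model, GEE or repeated-measures analysis.

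**The concern.** Scores from one woman at different visits are correlated. The Mann–Whitney U test assumes two independent samples, and ordinary linear regression assumes independent residuals. Applied to repeated scores from the same women, both give wrong standard errors, and the direction depends on the term. Comparisons within women (baseline against T-3, time, group-by-time) look less precise than they are. A group effect averaged over visits looks more precise than it is.

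Depression is the primary effectiveness outcome, and the regression is its only stated longitudinal analysis. The results are meant to inform a later full-powered trial, so intervals of the wrong width would be carried forward. There is a second, conditional risk. If the baseline-to-T-3 rows are run within each arm, a significant improvement in the START arm could be taken as evidence of efficacy, although it does not estimate the difference from standard care.

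**Working it through.** **Inputs.** Section 2.5 gives 72 evaluable women and section 2 gives 1:1 allocation, so n = 72/2 = 36 per arm. The recruitment figure agrees: 72/0.80 = 90. Table 3 gives four visits for the regression outcomes. The plan states no within-woman correlation ρ, so there is no figure of its own to reproduce on this point. *Assumption:* equal correlation between any two visits, ρ = 0.3, 0.5 or 0.7, with scores in SD units.

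**Baseline against T-3, same 36 women**

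- Unpaired SE = √(2/n) = √(2/36) = 0.236.
- Paired SE = √(2(1−ρ)/n) = 0.197 / 0.167 / 0.129.
- Ratio = 1/√(1−ρ) = 1.20 / 1.41 / 1.83.

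At ρ = 0.5 the smallest observed change reaching p < 0.05 is about 1.96 × 0.236 = 0.46 SD unpaired, against 1.96 × 0.167 = 0.33 SD paired. The ratio does not depend on n, so it is the same within one arm or over both.

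**Ordinary regression on four stacked scores per woman (true SE divided by reported SE)**

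- Time or group-by-time slope: √(1−ρ) = 0.84 / 0.71 / 0.55. At ρ = 0.5 the effective critical value is 1.96/0.71 ≈ 2.77, a true level of about 0.6%.
- Group main effect, no interaction: √(1+3ρ) = 1.38 / 1.58 / 1.76. At ρ = 0.5, 1.96/1.58 = 1.24, a true level of about 22%.
- Group term with a linear group-by-time term, visits coded 0 to 3. The group term is then the difference at visit 0. Apart from a common factor, its reported variance is 1/4 + 1.5²/5 = 0.70 and its true variance is (1+3ρ)/4 + 1.5²(1−ρ)/5 = 0.70 + 0.30ρ. At ρ = 0.5 the SE ratio is √(0.85/0.70) = 1.10, so 1.96/1.10 = 1.78 and the true level is about 8%.
- Group term with categorical visits and group-by-visit terms: this is a contrast at one visit, one score per woman, so the level is about 5%.

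**Simulation under no effect** (4,000 runs per ρ, 36 women per arm, four visits, nominal 5%), percentage rejecting:

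| Test | ρ = 0.3 | ρ = 0.5 | ρ = 0.7 |
|---|---|---|---|
| Unpaired t, baseline vs T-3 | 1.9 | 0.8 | 0.05 |
| Mann–Whitney, baseline vs T-3 | 2.0 | 0.8 | 0.1 |
| Paired t | 4.4 | 5.0 | 4.6 |
| Wilcoxon signed-rank | 4.5 | 4.8 | 4.9 |
| Regression: time slope | 2.1 | 0.9 | 0.03 |
| Regression: group-by-time | 1.8 | 0.7 | 0.03 |
| Regression: group main effect, no interaction | 15 | 22 | 26 |

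At ρ = 0 every rate is about 5%, so the departures come from the correlation alone. The simulation agrees with the formulas.

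**The case against.** Five points can be made for the plan.

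1. *The randomised comparison is sound.* This stands. The between-group tests at T-2 and T-3 use one score per woman, so independent-samples tests are right there. Section 2.5 states the sample size for the difference between groups. A reader might infer that the trial's efficacy p-values are invalid as a whole; the documents do not support that.

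2. *General linear may mean the repeated-measures GLM in SPSS, the software named.* This is possible, although both places say regression. That procedure would handle the correlation, but it drops every woman with a missing visit, in a trial that plans for 20% attrition (18 of 90) and for 35% as a contingency in section 2.10. The wording needs settling under either reading.

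3. *The baseline-to-T-3 rows may mean change scores compared between arms.* Section 2.9 introduces these tests under between-group differences, and Mann–Whitney would then be correct. It is the less literal reading, because Table 3 lists the group comparison on its own line. It cannot be excluded, and the plan should say which is meant. No passage says that efficacy will be concluded from within-arm tests, so that risk remains conditional.

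4. *A false-positive rate near 22% is not the plan's error rate.* This also stands. It arises only for a pooled group main effect without interaction, a term the plan does not name. For the stated purpose, change over time, the error is conservative.

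5. *A condensed article leaves model details to the full protocol or SAP.* This is fair for covariance structure and model terms. It does not cover the naming of an unpaired test for what reads as a comparison within women.

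**Conclusion.** The point holds in a limited form. The firmest part is the Mann–Whitney U test in the baseline-to-T-3 rows (T-2 to T-3 for growth): read literally, it is the wrong test for paired scores. A t-test might be paired, but the rank alternative named beside it is not. The regression part is somewhat less certain, because the phrase could loosely cover a repeated-measures model; as written it contains no within-woman term.

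With the assumed exchangeable correlation of 0.3 to 0.7, the main harm is intervals that are too wide and lost sensitivity: a standard error 1.20 to 1.83 times too large for baseline against T-3, and true levels of about 2% to under 0.1% for time and group-by-time tests. Inflation to about 15% to 26% would occur only if a group main effect were fitted without an interaction. The regression concerns three outcomes, and the paired-score rows concern all six scale outcomes. The between-group tests and the feasibility and acceptability results are untouched.

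**What to change.** In section 2.9 and Table 3:

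- Replace the linear regression by a linear mixed model (MIXED in SPSS), with woman as the subject, visit as a categorical factor, group-by-visit terms and the baseline score as covariate. Include every woman with at least one post-baseline score.
- In the baseline-to-T-3 and T-2-to-T-3 rows, replace the present choice by a paired t-test or Wilcoxon signed-rank test. If a comparison of change scores between arms is meant, say so and keep Mann–Whitney as the rank alternative.
- State that efficacy conclusions rest on the between-group contrast and that within-arm changes are descriptive.

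The cost is wording and slightly more analysis work in the software already named. No extra participants or measurements are needed.
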